##### Secondary

Between‐group difference in the proportion of subjects experiencing response to depression treatment (defined as MADRS score decreased by ≥50%) from baseline to 6 months.

Between‐group difference in the proportion of subjects experiencing recovery from depression (MADRS score decreases to ≤10) (Zimmerman et al., 2004).

Between‐group difference in the changes in other scales and measures, such as Beck Depression Inventory (BDI) and the Symptom Checklist‐90 (SCL‐90), and changes in blood markers, including inflammatory biomarkers, between baseline and 6 months. See Figure 1 for the complete list of secondary outcomes and the time points for each outcome measure. The mean/median values are compared between the higher‐dose supplementation group and the lower‐dose supplementation group at baseline and at 6 months.

**FIGURE 1 fsn34417-fig-0001:**
[figure not shown]
Schedule of actualized and planned patient‐related activities, collection of baseline data, and the primary and secondary outcomes during the intervention and the follow‐up in the DepFuD study. BDI, Beck Depression Inventory; BRCS, Brief Resilient Coping Scale; CORE‐OM, Clinical Outcomes in Routine Evaluation Outcome Measure; DIAD, Diagnostic Interview for Atypical Depression; ESR, erythrocyte sedimentation rate; FFQ, Food frequency questionnaire; fS‐PTH, fasting parathyroid hormone; GAF, Global Assessment of Functioning Scale; HDL, high‐density lipoprotein; LDL, low‐density lipoprotein; LOT‐R, Life Orientation Test ‐ Revised 6‐item version; LS‐4, Life Satisfaction Scale; MADRS, Montgomery–Åsberg Depression Rating Scale; P‐ALT, plasma alanine aminotransferase; P‐K, plasma potassium; P‐Na, plasma sodium; PSS10, Cohen's Perceived Stress Scale; P‐T4, plasma free thyroxine; P‐TSH, plasma thyroid‐stimulating hormone; S‐25(OH)D, serum 25‐hydroxyvitamin D; S‐Ca, plasma calcium; SCID‐I and SCID‐II, Structured Clinical Interviews for DSM‐IV; SCL‐90, Symptom Checklist‐90; S‐hs‐CRP, serum high‐sensitivity C‐reactive protein; SOC, Sense of Coherence Scale; TADS, The Trauma and Distress Scale; TAS‐20, Toronto Alexithymia Scale; YSQ‐S2‐extended, Young Schema Questionnaire S2‐extended. 1) interleukin‐1 alpha (IL‐1α), interleukin‐1 beta (IL‐1β), interleukin‐1 receptor antagonist (IL‐1ra), interleukin‐4 (IL‐4), interleukin‐6 (IL‐6), interleukin‐8 (IL‐8), interferon‐γ‐inducible protein‐10 (IP‐10), monocyte chemoattractant protein‐1 (MCP‐1), chemokine RANTES (regulated on activation, normal T‐cell expressed and secreted), transforming growth factor alpha (TGF‐α), tumor necrosis factor alpha (TNF‐α), tumor necrosis factor beta (TNF‐β), and metabolomics analyses.

#### Outcomes for the follow‐up study at 18 months and at 6 years from baseline

2.3.2

Data collected with study questionnaire and blood sampling, and changes in the data during follow‐up. The complete list of outcomes and time points for each follow‐up outcome measure is presented in Figure 1. Outcomes are measured at 18 months and at 6 years from baseline. Mean/median values or proportions of subjects who experience a categorized outcome can be compared between the higher‐dose supplementation group and the lower‐dose supplementation group or based on other defined baseline or background characteristic at each time point.Data from the Finnish national registers. Data obtained from national registers are linked to DepFuD with the patient's consent.
Diagnoses derived from the data of Finnish Institute for Health and Welfare specialized care notification register (Hilmo) and the primary care notification register (Avohilmo).Diagnoses derived from the Finnish Cancer Registry.Statistics Finland's—Health–Causes of death register.Use of prescription medications, derived from Kela's (Finnish social insurance institution) drug registers.Registers of occupational pension institutes.

### Participant timeline

2.4

The six‐month VD RCT was implemented for each consenting subject who met the inclusion criteria for the intervention at the beginning of the study, and the study continues as a follow‐up study. The data collection for the RCT took place between November 2015 and December 2020. See Figure 1 for all actualized and planned patient‐related activities.

### Sample size

2.5

The target sample size was derived from the VD intervention power calculation and was based on between‐group change in the MADRS score. The primary sample size calculation for DepFuD project was made in 2015 based on a small effect size of 0.15, by which the effect of the VD supplement was estimated to be at a clinically significant level, considering its benefit–risk ratio. In a two‐tailed test, with randomization ratio 1:1, alpha = 0.05, and power = 0.95, a total of 1211 individuals per intervention group should have been recruited to the study (a total of 2422 subjects). With accounting for attrition of 25%, a total of *n* = 3028 subjects would have been needed.

The target sample size was adjusted in 2019. According to previous literature, in adult patients with depression, an estimated minimal clinically important change in MADRS score during treatment was 1.6–1.9 points (Duru & Fantino, 2008). For DepFuD, a minimum of 4‐point improvement in MADRS score was considered as clinically important. With alpha = 0.05, power = 0.90, a between‐group difference of 4 units for MADRS mean, and a MADRS standard deviation (SD) = 12, a total of 382 subjects (191 per group) are required. Calculation was performed with PASS (Power Analysis and Sample Size) Software (NCSS, LLC., Kaysville, Utah) by an experienced statistician. Considering an estimated attrition of 25%, the study aimed to recruit a total of *n* = 478 subjects. The between‐group difference in MADRS mean values, which guided the determination of target sample size, is analyzed as the primary outcome, while response to treatment (defined as usual by arbitrary ≥50% MADRS score decrease from baseline) serves as a secondary outcome.

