### Trial design

1.3

DepFuD starts with a 6‐month clinical trial using a double‐blinded, parallel‐group, randomized controlled superiority design among psychiatric adult outpatients with a 1:1 allocation ratio. The follow‐up will continue up to 6 years after the trial baseline. DepFuD employs a multidisciplinary approach, integrating psychiatry, epidemiology, public health science, physiology, and biomedicine.

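### The 25% attrition allowance was added to the required 382 instead of being taken from the number recruited, so the target of 478 covers only about 20% loss and leaves about 358 evaluable at 25%

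*Protocol article*

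**What the plan says.** Section 2.5 of the protocol article gives two sample size calculations. The current one, from 2019, uses these inputs: "With alpha = 0.05, power = 0.90", a "between‐group difference of 4 units for MADRS mean" and "a MADRS standard deviation (SD) = 12". It concludes that "a total of 382 subjects (191 per group) are required". The next step is the attrition allowance: "Considering an estimated attrition of 25%, the study aimed to recruit a total of" 478.

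The 2015 calculation, which the 2019 one replaced, has the same structure. It needed 2422 subjects, and then: "With accounting for attrition of 25%, a total of" 3028.

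Three other places bear on the point:

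- Section 2.13 restricts the primary analysis to randomised subjects who came to every intervention visit and have no missing primary outcome data. It also removes those who took more than 10 μg/day of vitamin D outside the study almost daily.
- Section 3.2 says that the ethics committee accepted the updated calculation and target in June 2020.
- Section 5.1 reports 281 subjects assigned to the RCT.

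**The concern.** Section 2.5 presents 382, 25% and 478 as one consistent chain, and they do not fit together. Attrition in its ordinary sense is the share of enrolled subjects who are lost, so the number to enrol is the required number divided by the share retained. Multiplying the required number by 1.25 instead treats the losses as a quarter of the subjects who remain. Nothing in the article defines the 25% in that way.

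The slip reaches the primary analysis because that analysis uses completers only, so each subject lost is one fewer analysed. What is at stake is whether the published target delivers the evaluable number and the power that the section attaches to it.

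**Working it through.** **Inputs (Section 2.5 unless noted):** difference 4; SD 12; alpha 0.05; power 0.90; required total 382 (191 per group); attrition 25%; target 478. Allocation is 1:1 (Section 1.3). The 2019 text does not repeat the sidedness. The 2015 text says "In a two‐tailed test, with randomization ratio 1:1", and a one-sided test would need only 155 per group (normal approximation), so two-sided is the reading that fits.

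**Step 1. Reproduce 382.** The standardised difference is 4/12 = 0.333. A two-sided two-sample t-test needs 190.10 per group, rounded up to 191, or 382 in total. The normal approximation gives 190 per group. The stated 382 is therefore the number that has to be analysed, with nothing yet allowed for loss.

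**Step 2. Reproduce 478.** 382 × (1 + 0.25) = 477.5, rounded up to 478. This matches exactly.

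**Step 3. Apply the stated attrition to the target.** 478 × (1 − 0.25) = 358.5, so about 358, or 179 per group. That is about 24 short of 382.

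**Step 4. Attrition that 478 does cover.** 1 − 382/478 = 0.201, or about 20%.

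**Step 5. Target that keeps 382 at 25% loss.** 382/0.75 = 509.3, rounded up to 510 for equal groups (255 per group). Check: 510 × 0.75 = 382.5. The difference from the target is 510 − 478 = 32 subjects.

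**Step 6. Power under the plan's own assumptions (difference 4, SD 12, two-sided 0.05).**

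| Evaluable | Per group | Power, t-test | Power, normal approximation |
|---|---|---|---|
| 382 | 191 | 90.1% | 90.3% |
| 358 | 179 | 88.2% | 88.4% |

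**Step 7. The 2015 figure, as a check on method.** 2422 × 1.25 = 3027.5, rounded up to 3028, again an exact match. Division gives 2422/0.75 = 3229.3, or about 3230 with equal groups. The same multiplication was used both times, so 478 is not a typing slip.

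**The case against.** The strongest reply is that the effect is small and nothing now turns on it. Power falls from 90.1% to 88.2%. Recruitment ended in June 2020 (Section 2.6), the month in which the committee accepted the revised target, and 281 were randomised, which is below 382 before any loss. This stands, and it limits the weight of the point. It does not make the stated chain of figures correct.

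A second reply is that the power loss depends on the assumed SD of 12. The baseline MADRS SD in Table 3 is 6.04. The article does not give the SD of the change, so any other value is an assumption. With 179 per group, power is at least 90% for any SD up to about 11.6, 96.5% at SD 10 and 99.3% at SD 8.5. This also stands: the 88% is conditional on the plan's SD. The shortfall in evaluable subjects does not depend on the SD.

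Third, 358 need not be the analysed number even at 25% attrition, because Section 2.13 also excludes users of off-study vitamin D. Section 5.1 counts 19 such RCT participants at baseline. The article does not say whether the 25% includes them, so 358 should be given as the figure before those exclusions.

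A reader might infer two further things that the article does not support:

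- **That the recruitment shortfall is understated.** The article gives no percentage of target reached and describes no shortfall, so there is no such statement to correct.
- **That 478 and 3028 should be replaced by 510 and 3230.** Section 2.5 reports what was aimed for in 2019 and what the 2015 calculation produced. The 2019 target was accepted by the committee and the 2015 total is superseded. Overwriting them would misreport the trial's history.

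**Conclusion.** The point holds as an arithmetic error of modest size. Section 2.5 multiplies 382 by 1.25 where its stated attrition calls for division by 0.75. The target of 478 therefore protects 382 evaluable subjects against about 20% loss, not 25%. At 25% it leaves about 358, with about 88% power in place of 90%. About 510 would have been needed.

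This rests on three assumptions: attrition means the share of recruited subjects lost, losses are equal in the two groups, and the plan's difference of 4 and SD of 12 apply. It takes no account of exclusions for off-study vitamin D use.

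A reader might go further and conclude that this error left the trial underpowered. That does not follow. The step from 382 to 358 costs under two points of power. Randomising 281 matters much more: under the same assumptions, power is about 79.5% even if all 281 are analysed.

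**What to change.** Add a sentence or two to Section 2.5 and leave the reported targets in place:

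- Keep 478 as the target that was set and accepted. State that it was obtained as 382 × 1.25, that at 25% attrition it yields about 358 evaluable subjects (179 per group) and about 88% power for a difference of 4 and SD of 12, and that about 510 (255 per group) would have been needed to retain 382.
- Say that 358 is the number before any further exclusions for off-study vitamin D use under Section 2.13.
- Leave the 2015 total of 3028 as reported. At most, note that the same method was used and that 2422/0.75 gives about 3230.
- Carry the same explanation into the results paper if it repeats the planned sample size.

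The cost is a text change only. It affects no enrolment, no data and no analysis.

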### Recruitment

2.6

DepFuD subjects are patients from the KUH Specific Catchment Area, who were referred to the recruitment sites' (KUH Department of Psychiatry, Central Finland Hospital Nova, and Mikkeli Central Hospital) outpatient clinics for treatment of depression. The recruitment period spanned from November 2015 to June 2020. When a referral arrived, the personnel evaluated whether the patient met the inclusion criteria (Table 1). Potential study participants were evaluated by several clinicians in different centers, and the exact number of patients assessed for eligibility was unknown. If deemed suitable based on the referral, the patient received a plain language statement of the DepFuD study along with an invitation for the initial appointment. Patient could pose questions to the researchers before deciding to participate and providing an informed, written consent. The consenting subjects were assigned, either to the intervention or to the follow‐up study by the study nurse, following inclusion and exclusion criteria (Table 1).

### Allocation

2.7

The process of allocation was independent of the enrollment personnel, and no personnel outside the research group took part in the allocation. The allocation sequence was created by AR with computer‐generated random numbers, and the coding for allocation was concealed in a sealed envelope, until intervention analyses were performed. Subjects who had given their consent and who were found suitable for the VD intervention were randomized to either the (1) higher‐dose VD supplementation group (100 μg/4000 IU of cholecalciferol per day) or the (2) lower‐dose VD supplementation group (10 μg/400 IU of cholecalciferol per day) (control group). Randomization was performed with stratified block randomization with a chosen block size of 10, which aimed to allocate the subjects to the intervention groups as evenly as possible. Randomization was conducted after the first study visit baseline examinations. After allocation to the RCT, participants who reported using a VD supplement outside the RCT were asked to discontinue the use.

### The intervention (an RCT) and the follow‐up

2.8

The study nurse administered a six‐month daily dose of VD supplement to RCT‐assigned subjects. The VD supplement was advised to be used daily for 6 months, regardless of the season. Prohibited parallel supplements are listed in Table 1. See Section 2.14.2 Harms for criteria for discontinuing the allocated intervention. No other criteria were specified for modifying allocated interventions. During the RCT, subjects had study visits at three and 6 months from baseline. Adherence was monitored by asking participants to return used tablet jars at 6 months and by counting the number of unused tablets.

After the six‐month RCT, DepFuD continues as a clinical follow‐up study with patients with depression. The follow‐up includes filling in questionnaire (18 months and 6 years after baseline), one interview (18 months after baseline), and a blood sampling visit (18 months after baseline). Standard clinical treatment, including the use of any psychiatric medication, is provided, regardless of the RCT or the follow‐up participation.

According to the Finnish nutrition recommendations, for adults, the lower limit of adequate total intake of VD supplementation is 10 μg/400 IU per day and the upper limit of safe intake is set at 100 μg/4000 IU per day (Finnish Food Authority, 2020). The selection of the comparator dose that is nationally recommended for the most population enables a safe and ethical assessment of potential dose responses.

### Blinding (masking)

2.9

The study participants, the study nurse, the care providers at the recruitment sites, and data analysts were blinded to allocation during the RCT. Each participant had an anonymous identification number. VD containers and all VD tablets (produced by Galena Pharma Ltd) were of identical appearance and were administered only after they had been irreversibly assigned to the participant. During the trial, the participants were not aware of their blood VD concentrations, which could indicate their assigned intervention. The researchers analyzing the primary outcome did not have access to the data until the RCT ended. The study nurse informed the attending physician in the case of abnormal plasma calcium (P‐Ca) or serum parathyroid hormone, possibly indicating pathological VD metabolism. Side effects or toxicities were unlikely, as the upper intake level of safe use for adults was set at 100 μg of vitamin cholecalciferol/ergocalciferol per day (4000 IU/day) (European Food Safety Authority, 2016). There were no specific requirements for circumstances under which unblinding subject's allocated intervention during the trial would have been permissible but if required, the corresponding investigator would have had access to group allocations.

### Data collection, management, and analysis

2.10

Study data are collected through self‐administered paper or online questionnaires, clinical interviews, health examinations, and blood samples. Subjects were also asked for their consent to the use of their medical record data for the study. See Figure 1 for the schedule for the data collection and for the complete list of used clinical scales and measures, clinical interviews, health examinations, and analyzed biomarkers. There are no specific plans to minimize loss to follow‐up. Separate data were not collected from those who refused to participate in the study, and DepFuD data collection ends if subject discontinues participation.

The clinical scales, measures, and interviews used are internationally validated and established. A description of the study instruments along with their expected reliability and validity is presented in Table 2. Preexisting Finnish translations are used. Subjects had the opportunity to fill out the study questionnaire at their psychiatric care unit at baseline, 3, and 6 months. At 18 months, subjects received mailed questionnaires with an information letter and a return envelope. At the 6‐year follow‐up, subjects can choose whether to fill out either the mailed questionnaire or an online questionnaire. The study nurse conducted health examinations at baseline, 3 months, 6 months, and 18 months, measuring weight, height, waist circumference, hand grip strength, and blood pressure. Blood samples were taken at these same intervals.

**TABLE 2 fsn34417-tbl-0002:** The description of the DepFuD study instruments along with their expected reliability and validity.

Instrument	Description
Clinical interviews	
Montgomery–Åsberg Depression Rating Scale (MADRS)	A 10‐item diagnostic questionnaire with adequate inter‐rater reliability and validity to measure the severity of depressive symptoms in patients with mood disorders. Developed to be sensitive to change in depressive symptoms and to differentiate between responders and nonresponders to antidepressant treatment. Each item is rated 0–6 and items are summed (overall score range 0–60, higher score indicating more severe depression) (Montgomery & Åsberg, 1979). A score decrease to ≤10 is defined as a remission and a score decrease by 50% from baseline is defined as a response to treatment (Zimmerman et al., 2004).
Diagnostic Interview for Atypical Depression (DIAD)	A structured interview for identifying the symptoms of atypical depression (mood reactivity, hypersomnia, leaden paralysis, hyperphagia, and rejection sensitivity) (Terman et al., 1998a). Each item is scored according to the scoring instructions of the instrument (Terman et al., 1998b). Adequate reliability and validity. Recommended instrument for confident assessment of depression with atypical features (Terman et al., 2003)
Global Assessment of Functioning Scale (GAF)	An interviewer‐used scale to rate subjectively the social, occupational, and psychological functioning of an individual on a hypothetical continuum of mental health and illness (scale range 1–100, lower score indicating more disablement and more severe symptoms within the dimension that is most adversely affected) (American Psychiatric Association, 2000). Widely used in clinical practice, despite rather poor inter‐rater reliability and poor discriminant validity with disease severity and physical limitations in a clinical setting for outpatients with depression (Grootenboer et al., 2012).
Structured Clinical Interview for DSM (SCID‐I and SCID‐II) edition DSM‐IV	A semi‐structured interview for making psychiatric diagnoses according to the diagnostic criteria from the Diagnostic and Statistical Manual of Mental Disorders (DSM‐IV). SCID‐IV for DSM‐IV has been superseded by SCID‐5 for DSM‐5, but SCID‐IV is still usable for research purposes. Following the multiaxial organization of DSM‐IV, SCID‐I is used for collecting information for Axis I disorders (major mental disorders) and SCID‐II for Axis II disorders (personality disorders) (Columbia University, Department of Psychiatry, 2018). Adequate psychometric inter‐rater and test–retest reliability for both Axis I and Axis II disorders (Zanarini et al., 2000).
Clinical scales and measures	
Beck Depression Inventory (BDI)	A 21‐item self‐reported scale for the measurement of cognitive and somatic aspects of depression and symptom intensity (scale range 0–63, higher score indicating more intense symptoms) (Beck, 1961). A good discriminant validity as a measure of depression and to reflect the severity and time frame of depressive symptoms in a Finnish population (Aalto et al., 2012).
Sense of Coherence Scale (SOC)	A 13‐item self‐reported questionnaire to assess life‐views; comprehensibility, manageability, and meaningfulness, and abilities to maintain and develop health. Items, part of which (1, 2, 3, 7, and 10) are negatively formulated, are rated with a 7‐point Likert scale with response options relevant to each item (score range 7–91, higher scores indicate greater levels of sense of coherence) (Antonovsky, 1993). High structural validity and high temporal stability in a population‐based Finnish cohort (Feldt et al., 2007).
15‐D Questionnaire	A self‐administered questionnaire to assess the different dimensions of current health‐related quality of life (mobility, vision, hearing, breathing, sleeping, eating, communication, elimination, usual activities, mental function, discomfort and symptoms, depression, distress, vitality, and sexuality). Each of the 15 items is scored on a 5‐point scale (1 indicating the best and 5 the worst possible situation). The points are used to calculate both an overall index value and a profile scoring of the dimensions on a scale of 0–1 (0 = dead, 1 = perfect health). Index value is calculated by weighting the questions with coefficients that describe the values of the population. The SPSS syntax for deriving 15‐D scores and replacing missing 15‐D data was obtained from the author. A generalizable, valid, and reliable instrument with a good discriminatory power in Western‐type societies (Sintonen, 2001).
Cohen Perceived Stress Scale (PSS10)	A 10‐item self‐reported scale to measure the degree to which situations in one's life are appraised as stressful during the last month. Score is obtained by reversing responses (0 = 4, 1 = 3, 2 = 2, 3 = 1, and 4 = 0) to the four positively stated items (4, 5, 7, and 8) and then summing across all scale items (score range 0–40, higher score indicating more stress) (Cohen & Williamson, 1988). Psychometrically validated for assessment of perceived stress in Swedish and similar populations (Nordin & Nordin, 2013).
Life Satisfaction Scale (LS‐4)	A 4‐item Allardt's self‐reported Likert scale to measure life satisfaction (range 4–20; satisfied 4–6; intermediate 7–11; and dissatisfied 12–20) with three life assessments in 5‐point scale (happiness, interestingness, and easiness of life) and one assessment in 4‐point scale (perceived loneliness). A well‐accepted and successfully used instrument for screening, monitoring, and predicting subsequent mental health among e.g. depressive patients and general populations (Koivumaa‐Honkanen et al., 2011).
Life Orientation Test‐Revised (LOT‐R)	A 6‐item self‐reported scale (without its filler items) to assess the optimistic and pessimistic dimensions of one's expectations of the future. Items are rated on a 5‐point scale. After reversing the scoring (0 = 4, 1 = 3, 2 = 2, 3 = 1, and 4 = 0) for the three negatively worded items (2, 4, and 5), item scores are totaled to yield an overall score (scale range 0–24, higher score indicating greater overall optimism) (Scheier et al., 1994). The scale has been translated and used in a Finnish population (Saari, 2019). An accurate tool for assessing individual differences on the pessimism–optimism continuum (Chiesi et al., 2013).
Young Schema Questionnaire (YSQ‐S2‐extended)	A 90‐item YSQ‐S2‐extended measures 18 early maladaptive schemas grouped under five schema domains: disconnection and rejection (includes five schemas), impaired autonomy (four schemas), impaired limits (two schemas), other‐directedness (three schemas), and overvigilance and inhibition (four schemas). The questionnaire contains 90 self‐statements (five for each schema), which respondents are asked to rate on a Likert scale ranging from 1 (completely untrue of me) to 6 (describes me perfectly). Scores for each early maladaptive schema subscale are based on the mean of the five schema statements. Total scores for schema domains are calculated as the total sum of the schema scores for each domain (Young, 1998; Young & Brown, 1994). The factor structure and psychometric properties of the Finnish version of the YSQ‐S2‐extended have been established (Saariaho et al., 2009).
Clinical Outcomes in Routine Evaluation Outcome Measure (CORE‐OM)	A 34‐item nondiagnosis‐specific self‐reported instrument with good reliability, validity, and sensitivity to change. Designed to monitor changes in psychiatric patients through the course of outpatient treatments. The maximum score is 136 and the mean score is obtained by dividing the number of total points by the number of answered questions (higher scores indicate more problems) (Evans et al., 2002). The Finnish version of CORE‐OM is psychometrically sound and is recommended for use in mental health settings (Honkalampi et al., 2017).
Toronto Alexithymia Scale (TAS‐20)	A 20‐item self‐administered questionnaire for screening the three components of alexithymia: difficulty identifying feelings, difficulty describing feelings, and externally oriented thinking. Items, five of which are negatively keyed, are rated with a 5‐point Likert scale and the score is the sum of responses to all 20 items. Cut‐off scoring: ≤51 = non‐alexithymia, ≥61 = alexithymia, and scores of 52 to 60 = possible alexithymia. In addition, the score for the three alexithymia components is calculated by using factor handling (Bagby et al., 1994). The questionnaire has been validated in several populations and languages, including Finnish (Joukamaa et al., 2001).
Brief Resilient Coping Scale (BRCS)	A 4‐item self‐reported measure designed to capture tendencies to cope with stress in a highly adaptive manner. Each item is scored from 1 to 5 (scale range 4–20, higher score indicating higher resilient coping). Developed originally in samples of adults with rheumatoid arthritis. Adequate internal consistency and test–retest reliability (Sinclair & Wallston, 2004).
The Trauma and Distress Scale (TADS)	The Finnish version of a 43‐item self‐reported questionnaire for assessment of multiple types of childhood trauma and distressing experiences. Items are rated with a 5‐point Likert scale (higher points indicate more frequent adversities) and the scores for the five TADS domains (emotional neglect, emotional abuse, physical neglect, physical abuse, and sexual abuse) are calculated by summing the respective items (final score range 0–20). A valid, reliable, and clinically useful instrument for assessing retrospectively reported childhood traumatization in a Finnish population (Salokangas et al., 2016).
Symptom Checklist‐90 (SCL‐90)	A 90‐item self‐reported questionnaire designed to measure self‐reported symptom intensity on nine different subscales (somatization, obsessive–compulsive, interpersonal sensitivity, depression, anxiety, hostility, phobic anxiety, paranoid ideation, and psychoticism). Items are rated on a 5‐point Likert scale of distress (higher points indicate higher distress) and a mean score for each subscale is calculated to be compared with population means. (Derogatis et al., 1973) A psychometrically valid and reliable instrument for psychiatric screening and outcome measuring in a Finnish population (Holi, 2003).

Clinical routine laboratory measures (fasting plasma blood glucose, fasting plasma triglycerides, total cholesterol, low‐density lipoprotein, and high‐density lipoprotein, plasma albumin, plasma alanine aminotransferase (P‐ALT), plasma creatinine, plasma thyroid‐stimulating hormone (P‐TSH) and plasma free thyroxine (P‐T4), serum high‐sensitivity C‐reactive protein (S‐hs‐CRP), erythrocyte sedimentation rate (ESR), serum 25‐hydroxyvitamin D (25(OH)D), red blood cell folate, plasma vitamin B12, plasma sodium (P‐Na) and plasma potassium (P‐K), fasting parathyroid hormone (fS‐PTH), and plasma calcium) were analyzed immediately, while experimental biomarkers and the whole blood sample for DNA analysis will be analyzed later in one batch. Data from blood sample analyses are electronic. Blood sample tests were provided by the Eastern Finland Laboratory Centre Joint Authority Enterprise (ISLAB) with the same procedures as it would occur as part of patient care without the study. Blood after centrifugation (serum and plasma) for the experimental biomarkers and the whole blood sample for DNA analysis are stored at −80°C. Experimental biomarkers in serum will be measured using multiplex biomarker panel. A DNA sample is only taken during the first blood sampling (whole blood sample).

